**4.2.4 Termination criteria:**

1. Subjects who withdraw informed consent and request early exit;

2. Medical imaging indicates disease progression;

3. Becoming pregnant during the study;

4. Intolerable toxicity after two dose adjustments; and

5. Other circumstances that necessitate study exit, as deemed by the investigators.

**4.3 Enrollment**

Competitive enrollment across the sites.

**5. Treatment Prescription**

Treatment is prescribed by the treating physician. Patients are selected for treatment with apatinib mesylate tablets in accordance with the entry criteria. Participation is voluntary.

See apatinib mesylate tablets package insert for prescribing information.

**6. Study Procedures and Data Collection**

**6.1 Data collection plan**

Safety data will be collected from the date of signing the ICF through 30 days after the last dose.

All AEs are recorded on a case report form (CRF) from the date of signing the ICF through the end of the study.

The incidence and severity of AEs will be monitored and evaluated in accordance with NCI CTCAE 4.0.

Each patient is expected to attend all scheduled visits so as to record specific data at different time points during the visits.

**6.2 Screening visit**

The screening visit should be completed within 14 days before treatment cycle 1 and will include electrocardiography (ECG) and chest and abdomen CT or magnetic resonance imaging (MRI). Within 7 days before treatment, a medical history will be obtained, and tests, including ECOG PS score, physical examination, vital signs, CBC, urinalysis, stool test, gastroscopy (as needed), echocardiogram, liver and kidney function, blood electrolytes, coagulation, tumor marker (carcinoembryonic antigen (CEA)), pregnancy test (as needed), and QoL assessment, will be conducted.

**6.3 Visits during the treatment period (cycles 1-3)**

During the treatment period (cycles 1-3), blood pressure will be measured three times per week during the first 2 weeks of treatment and then twice per week thereafter; CBC, urinalysis, and stool tests will be performed every 2 weeks; liver and kidney function and electrolytes will be measured every 4 weeks. ECOG PS score, physical examination, coagulation (prothrombin time (PT), APTT, thrombin time (TT), fibrinogen (Fbg), and ECG will be recorded during each cycle. AEs will be monitored and recorded as they occur.

Drug safety and objective response, QoL score, and CEA will be evaluated at the end of cycles 2 and 3.

**6.4 Additional visits**

Beginning with cycle 4, blood pressure will be measured at least once per week; CBC, urinalysis, stool tests, liver and kidney function, and electrolytes will be measured every four weeks. ECOG PS score, physical examination, coagulation (PT, APTT, TT, Fbg), and ECG will be recorded during each cycle. AEs will be monitored and recorded as they occur.

Drug safety and objective response, QoL score, and CEA will be evaluated every 2 cycles and at the end of treatment (if > 2 weeks since the last imaging date).

**6.5 Follow-up visits**

Patients will enter the posttreatment follow-up period after the last dose of apatinib. Patients who discontinue treatment due to PD should be followed up for survival. Patients who discontinue treatment or withdraw from the study due to reasons other than PD will undergo tumor evaluations every eight weeks until PD, death, the end of the study, or intolerable toxicity. Patients who have no significant adverse reactions after disease progression and are willing to continue apatinib treatment will be closely monitored and followed up for survival.

The following important parameters should be closely monitored and recorded during the follow-up period: time to PD, time of death (phone follow-up is acceptable; a record should be maintained), and other treatments and remedies.

**6.6 Follow-up of adverse events**

Patients will be closely followed up after the last dose for any new AE. Any unresolved AE at the time of apatinib discontinuation will be followed up until it is resolved, has returned to the baseline level, or is no longer clinically relevant.

**6.7 Procedures for patients who discontinue follow-up**

Patients may withdraw informed consent at any time and for any reason. Study withdrawal is considered only if the patient declines follow-ups to monitor his/her survival; otherwise, the patient is still considered in the study. The investigators will make every effort to contact the patients regularly to check their health status, at the very least survival.

**7. Data Management**

**7.1 Data entry and modification**

Data entry and management will be the responsibility of an independent data management agency. The clinical coordinator will use HRTAU-EDC software for clinical data entry and management to ensure data accuracy and timely entry. In the case of any question about the data in the database, the data administrator, medical manager, and study monitor may send an inquiry via the system to the investigator, who will promptly review and answer any questions.

**7.2 Database security**

After data review and verification, the PIs, sponsor, and statisticians will lock the database. No modification to data files will be allowed after locking.

**8. Safety Evaluation**

**8.1 Monitoring adverse events**

An AE is defined as any untoward medical event that occurs after the subject or participant receives a drug or treatment regimen, regardless of the causal relationship to the treatment.

AEs may be any unpleasant signs (including abnormal laboratory tests), symptom, or illness with a temporal relationship or unrelated to the use of apatinib, regardless of whether they are considered related to apatinib.

According to regulations, untoward events that occur before or after treatment are also considered AEs. Therefore, safety monitoring of AEs and SAEs will begin from study entry (signing the ICF) through the end-of-study visit.

**8.2 Rating adverse events**

AEs will be rated as 0-5 in accordance with NCI CTCAE 4.0 (see Annex 2). Any AE not listed in NCI CTCAE 4.0 will be rated based on the following criteria:

Grade I (mild): discomfort, with no effect on daily activities;

Grade Ⅱ (moderate): discomfort that reduces or affects daily activities;

Grade Ⅲ (severe): unable to work or engage in daily activities; and

Grade IV (life-threatening): disability or death.

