**9.2 Analysis variables**

**9.2.1 Primary measures**

AEs will be coded according to MedDRA, and each AE will be assigned a system organ classification (SOC) and a preferred term. The severity of AEs will be evaluated in accordance with NCI CTCAE 4.0.

The primary endpoints will include the incidence and severity of AEs.

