**9.3.2 Primary analyses**

The primary endpoints will include the incidence, severity, correlation, risk factors, measures taken, and outcomes of each AE.

⚫ Study period, drug exposure

SS will be used as the study population to describe the dosing rate, actual dose intensity, and treatment discontinuation and the cause.

⚫AEs

AEs will mainly be described with descriptive statistics. Laboratory tests that are normal before treatment but abnormal after treatment or abnormal before treatment and worsen after treatment will be described, and their relation to apatinib mesylate tablets will be indicated.

All other AEs will be listed per subject. Treatment-emergent SAEs, death, and the incidence and 95% CIs for drug discontinuation due to an AE will be calculated. AEs will be summarized per SOC and preferred terms.

The incidence, severity, correlation, risk factors, measures taken, and outcomes of important known AEs (hypertension, bleeding, proteinuria/renal toxicity, and HFS) will be monitored and recorded.

The incidence, severity, correlation, risk factors, measures taken, and outcomes of important potential AEs (grade 3/4 diarrhea, gastrointestinal fistula/perforation, wound healing complications, decreased left ventricular ejection fraction/heart failure, thrombosis/embolization, liver toxicity, hypothyroidism) will be monitored and recorded.

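### The severity scale for AEs not listed in CTCAE stops at grade IV and puts death in it, while the main scale runs to 5

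*Protocol*

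**What the plan says.** Section 8.2 (Rating adverse events) sets two scales.

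- The main rule: "AEs will be rated as 0-5 in accordance with NCI CTCAE 4.0".
- A fallback: "Any AE not listed in NCI CTCAE 4.0 will be rated based on the following criteria". Four levels follow. Grades I and II are mild and moderate discomfort. Grade III is severe, described as "unable to work or engage in daily activities; and". The last is "Grade IV (life-threatening): disability or death".

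Section 9.2.1 (Primary measures) makes severity part of the primary endpoint: "The primary endpoints will include the incidence and severity of AEs". For grading it names one scale only: "The severity of AEs will be evaluated in accordance with NCI CTCAE 4.0". The fallback scale is not mentioned there. Sections 3.4 and 9.3.2 also list severity under the primary endpoint.

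**The concern.** The two scales share grade numbers, but their top ends do not correspond. An investigator who follows Section 8.2 has a level above 4 for a fatal AE that CTCAE lists, and none for a fatal AE that it does not list. The second event must be graded IV, together with survived life-threatening events and disability.

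What is at stake is the meaning of grade 4 in a primary measure. For listed AEs, level 4 is separated from the level above it. For unlisted AEs, it mixes fatal and non-fatal events. A severity summary that takes the recorded grades at face value would carry both meanings under one label.

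This is more than detail left to an analysis plan. The grade is recorded at the site, on the CRF, under the protocol's instruction. A later plan could recode it, but the instruction itself would still misclassify the event.

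**Working it through.** There is no published figure to reproduce, so the check is a comparison of the two scales in Section 8.2, followed by a search for text that would reconcile them.

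**Step 1: the levels side by side.**

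| Level | Main scale (CTCAE 4.0) | Fallback scale (unlisted AEs) |
| --- | --- | --- |
| 0 | present | not defined |
| 1 | present | I, mild |
| 2 | present | II, moderate |
| 3 | present | III, severe |
| 4 | present | IV: life-threatening, disability and death together |
| 5 | present | not defined |

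The main scale has six levels and the fallback has four. The missing level 0 does no harm to the grading of an event that has occurred. The missing level 5 matters because the fallback names death explicitly and puts it in IV.

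**Step 2: is it reconciled elsewhere?** Sections 3.4, 6.1, 8.3, 8.5, 9.2.1, 9.2.2 and 9.3.2 were read for a grade V on the fallback scale, or for a rule that maps its fatal events to grade 5. None has either. Section 8.5 does show that the protocol can separate the three notions, since it lists death, life-threatening events and permanent or severe disability as distinct seriousness criteria. Section 8.2 merges them into one grade.

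**Step 3: effect on counts.** Let *d* be the number of fatal AEs graded on the fallback scale. Compared with a scale that has a grade V for death:

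- events at grade 4: + *d*
- events at grade 5: − *d*
- events at grade 3 or higher: + *d* − *d* = 0

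The protocol gives no value for *d* and nothing to derive it from. Zero is possible, and in that case no count changes.

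**Step 4: are the deaths still visible?** Yes. Section 8.3 records the outcome of each AE, Section 8.5 makes any event leading to death an SAE, Section 9.2.2 lists mortality as its own safety measure, and Section 9.3.2 names death in the planned analysis. A fatal unlisted AE can be identified from these whatever its grade.

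**The case against.** The strongest reply is that this is a loosely worded fallback clause with little practical effect. The event's fatal outcome is recorded in several other places, no incidence estimate changes, and tabulation detail may sit in an analysis plan that is not shown. Most of that stands, and it limits the size of the point. It does not remove it, because the stated rule still gives the wrong label and nothing in the protocol corrects it.

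The same reply disposes of several stronger readings that a reader might infer:

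- *Fatal new or unusual events would be hidden.* They would not, for the reasons in step 4. Being absent from the CTCAE list is also not the same as being new or unusual.
- *Grade 3/4 rates would be inflated and a grade 5 row undercounted.* The planned analyses specify neither an overall grade 3/4 rate nor a grade 5 row. The only grade 3/4 category there is attached to diarrhea: "important potential AEs (grade 3/4 diarrhea, gastrointestinal fistula/perforation". The overall grade 3/4 rates of 60.23% and 41.76% in Section 1.1.3.3 are results of the earlier phase III study, not a table planned here.
- *Grade 5 AEs would fail to reconcile with mortality.* Mortality in Section 9.2.2 carries no restriction on cause, and Section 8.5 has death from disease progression reported as an SAE. Nothing says that the two counts should agree.
- *A life-threatening event that is survived without disability has no grade.* The label of Grade IV already covers it.
- *A number can be put on it.* Assuming that 0.1% to 0.5% of the 2000 patients have such an event would give 0.001 × 2000 = 2 to 0.005 × 2000 = 10 events, but nothing in the protocol supports those shares, and the range leaves out zero.

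**Conclusion.** The inconsistency is real and minor. Section 8.2 grades a fatal unlisted AE as 4 beside a main scale that goes to 5, so grade 4 is not uniform across events in a primary measure. The harm is misclassification between the top two grades. No death goes unrecorded, and counts of grade 3 or higher are unaffected. The size is unknown and possibly nil.

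One assumption should be stated. The protocol does not itself spell out that grade 5 on the main scale means death. It leaves this to CTCAE 4.0 in Annex 2, which is not reproduced. The mismatch between a scale of 0 to 5 and one of I to IV with death inside IV is visible without that assumption. It is needed only to say that the new top level should be the one for death.

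**What to change.** In Section 8.2, define fallback Grade IV as life-threatening or disabling and non-fatal, and add Grade V as death related to the AE, after checking the wording against Annex 2. Put the same definitions in the CRF guidance. If any fatal AE has already been graded IV on the fallback scale, recode it to V from its recorded outcome.

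The cost is a change to one line of the protocol, a matching change to the CRF guidance, and a query on existing fatal fallback events, of which there may be none. No new data are needed, and no dose, treatment or follow-up rule is touched.

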**8.3 Recording adverse events**

The name, severity, time of onset, duration, treatment measures, and outcomes of each AE that occurs during the study will be recorded and truthfully reported on a CRF. Abnormal laboratory tests will be recorded on a CRF, repeated at least once per week, and followed up until resolution or the end of the study.

Any AEs that occur within 30 days after the last dose will be reported and recorded.

**8.4 Determining the relationship between adverse events and apatinib mesylate tablets**

The correlation between any AE and apatinib will be classified as “definitely”, “probably”, “possibly”, “unlikely”, and “unrelated” (see Table 1). The first three categories indicate that an AE is related to apatinib and will be included as the numerator when calculating the incidence of AE. All subjects will be included as the denominator for safety evaluations.

Table 1. Criteria for Determining the Relationship between Adverse Events and Apatinib Mesylate Tablets

| Criteria | Definitely | Probably | Possibly | Unlikely | Unrelated |
| --- | --- | --- | --- | --- | --- |
| Reasonable temporal relationship | Yes | Yes | Yes | Yes | No |
| Known drug reaction | Yes | Yes | Yes | No | No |
| Improvement after discontinuation | Yes | Yes | Yes or No | Yes or No | No |
| Recurrence after re-administration | Yes | ? | ? | ? | No |
| Additional possible explanations | No | No | No | Yes | Yes |

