**Results:** After randomization, six untreated patients were excluded from analyses. A total of 267 randomized patients received at least one dose, including 176 patients in the experimental group and 91 patients in the placebo control group. Baseline data were comparable between the two groups. As of May 23, 2013, full analysis set (FAS) analysis, without considering crossover, showed that the mOS was 6.5 months in the experimental group and 4.7 months in the control groups, indicating that apatinib significantly extended survival by 1.8 months (*P* = 0.0149). Per-protocol set analysis indicated that the mOS was 7.6 for the experimental group and 5.0 months for the placebo control group, indicating that apatinib significantly extended survival by 2.6 months (*P* = 0.0027). When considering crossover, the mOS was 4.5 months in the control group after the data were adjusted for subjects who crossed over to the experimental group and was 2.0 months longer in the experimental group (HR = 0.646, *P* = 0.006), indicating that apatinib extended the mOS in the experimental group. The mPFS was 2.6 months in the experimental group and 1.8 months in the control group (*P* < 0.0001); the ORR was 2.84% in the experimental group and 0.00% in the control group (*P* = 0.1695); and the DCR was 42.05% in the experimental group and 8.79% in the control group (*P* < 0.0001). No significant between-group difference was observed in the change in QoL score (*P* > 0.05). For safety, apatinib was well tolerated in the experimental group, and the type and incidence of AEs were consistent with the findings in the apatinib phase II clinical study and with those for similar drugs on the market. Common AEs were leukopenia, neutropenia, thrombocytopenia, proteinuria, hypertension, HFS, fatigue, loss of appetite, diarrhea, and hoarseness; no unexpected AEs were observed. The incidence rate of AEs was 98.30% in the experimental group and 90.11% in the control group (*P* = 0.0038); the incidence of grade 3/4 AEs was 60.23% in the experimental group and 41.76% in the control group (*P* = 0.0000); the incidence of serious adverse events (SAEs) was 15.34% in the experimental group and 16.48% in the control group (*P* = 0.8598); and the incidence of drug-related SAEs was 6.25% in the experimental group and 6.59% in the control group (*P* = 1.0000). Most AEs were expected, tolerable, reversible, and controllable.

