**3.4 Study endpoints**

**Primary endpoint:**

⚫ **Safety:**

The incidence, severity, correlation, risk factors, measures taken, and outcomes of all AEs will be closely monitored and recorded in accordance with NCI CTCAE 4.0. Special attention will be paid to specific AEs, such as hypertension, bleeding, proteinuria, and HFS.

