**9.2.2 Secondary measures**

**a. Safety measures**

⚫ The incidence of treatment-emergent AEs

⚫ The incidence of AEs leading to treatment discontinuation and/or early withdrawal

⚫ The incidence of SAEs and drug-related SAEs

⚫ Mortality

⚫ Drug discontinuation due to AEs

⚫ Changes in vital signs after treatment (heart rate, blood pressure, temperature, respiration)

⚫ Changes in physical examination results after treatment

⚫ Clinical laboratory abnormalities

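### Section 8.4 limits the numerator of AE incidence to drug-related events, contradicting the all-cause AE primary endpoint

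*Protocol*

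**What the plan says.** Section 8.4 sorts each AE into five causality categories and then fixes a calculation rule: the definitely, probably and possibly related categories "will be included as the numerator when calculating the incidence of AE". The next sentence sets the denominator: "All subjects will be included as the denominator for safety evaluations".

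Other sections describe AE incidence without any limit on causality:

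- Section 8.1 defines an AE as any untoward event after treatment, "regardless of the causal relationship to the treatment".
- Section 3.4 gives the primary endpoint: "The incidence, severity, correlation, risk factors, measures taken, and outcomes of all AEs will be closely monitored and recorded". Relatedness, which the protocol calls correlation, is one attribute in that list and not a condition for being counted.
- Section 9.2.1 states: "The primary endpoints will include the incidence and severity of AEs". It adds no restriction and gives no numerator of its own. Section 9.3.2 repeats the longer list for each AE.
- Section 9.2.2 lists among the secondary safety measures "The incidence of treatment-emergent AEs", unrestricted, and names SAEs and drug-related SAEs as two quantities.

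Section 9.1 defines the Safety Set as enrolled subjects with at least one dose and at least one safety evaluation.

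**The concern.** The term that 8.4 restricts to related events is the same term that names the primary endpoint. Two statisticians could each follow this protocol and report different primary results, one related-only and one all-cause. This is not a detail left to the SAP: section 9.3.1 says that the SAP is to be based on the protocol, so it would inherit the rule or have to overrule it.

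A related-only count is a subset of the all-cause count, so any distortion runs in the favourable direction. It also makes the primary figure depend on judgements of cause in an open-label, single-arm study with no control group to check them. Section 1.2 describes the study as a post-marketing safety commitment required by the regulator. The events that matter most for that purpose include those not yet known to be drug reactions.

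**Working it through.** **1. The passages side by side**

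| Place | What is counted | Limited to related events? |
| --- | --- | --- |
| 8.1 | definition of an AE | no |
| 3.4 | primary endpoint, all AEs | no |
| 9.2.1, 9.3.2 | primary measure and its analysis | no |
| 9.2.2 | treatment-emergent AEs | no |
| 9.2.2 | SAEs, and separately drug-related SAEs | both given |
| 8.4 | numerator of AE incidence | **yes** |

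Section 8.4 is the only entry that states a numerator, and the only one that applies a related-only limit to a measure not labelled as drug-related.

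**2. What Table 1 lets into the numerator**

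All three counted columns (definitely, probably, possibly) require a known drug reaction and the absence of any other possible explanation. Read literally:

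- an unexpected event fails the first requirement;
- an event that the cancer could explain fails the second. Bleeding (named in 3.4) and gastrointestinal perforation (named in 9.3.2) are plausible examples in gastric cancer.

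Neither kind of event could then enter the 8.4 numerator.

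**3. Reproducing the phase III figures (section 1.1.3.3; 176 apatinib, 91 placebo)**

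- All SAEs: 27/176 = 15.34%; 15/91 = 16.48%.
- Drug-related SAEs: 11/176 = 6.25%; 6/91 = 6.59%.
- Any AE: 173/176 = 98.30%; 82/91 = 90.11%.
- Grade 3/4 AEs: 106/176 = 60.23%; 38/91 = 41.76%.

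All agree with the stated percentages.

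**4. Illustration of the difference**

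SAEs are the only category with both an all-cause and a related rate. In the apatinib arm the ratio is 6.25/15.34 = 0.41 and the difference is 15.34 − 6.25 = 9.09 percentage points.

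**5. The any-AE and grade 3/4 rates**

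No related rate is given, so the effect turns on an unknown share *s*: the proportion of patients with such an event who have at least one that is judged related. The related-only rate is the all-cause rate times *s*. Assuming *s* between 0.5 and 1:

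- any AE: 98.30% × 0.5 = 49% up to 98.30% × 1 = 98%;
- grade 3/4: 60.23% × 0.5 = 30% up to 60.23% × 1 = 60%.

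The range runs from a halving to no change. The document does not narrow it.

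**6. Denominator**

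In phase III, 6 of 273 randomized patients were untreated (2.2%); on apatinib it was 181 − 176 = 5 of 181 (2.8%). If all subjects in 8.4 meant all enrolled subjects, a similar proportion here would change the rates only slightly.

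**The case against.** Section 8.4 deals with causality classification, while the analysis is set out in section 9, where nothing is limited to related events. All AEs go on the CRF (6.1, 8.3), and 9.3.2 plans per-subject listings and summaries by SOC and preferred term. So the events are not lost, and an analyst might simply follow section 9. This stands: the protocol contradicts itself and does not clearly fix a related-only endpoint. It does not remove the problem, because the one explicit numerator is the wrong one.

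Three stronger readings are tempting, and the documents do not support them.

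- *The primary rate will be reported far too low.* The 15.34% and 6.25% contrast concerns SAEs, a secondary measure for which 9.2.2 already plans both figures. For the any-AE rate the fall may be modest. Projecting the SAE figures to 2000 patients and comparing confidence intervals adds nothing, because the gap is one of definition and not of sampling.
- *Phase III shows that attribution cannot tell drug from placebo.* It is true that "the incidence of drug-related SAEs was 6.25% in the experimental group and 6.59% in the control group". But all-cause SAEs were no more frequent on apatinib (15.34% against 16.48%), so there was no excess to detect. The related shares, 11/27 (95% CI 22–61%) and 6/15 (16–68%), are very imprecise. The judgements were made double-blind, so they say nothing direct about open-label attribution.
- *The denominator is a serious conflict.* All subjects for safety evaluations can be read as the Safety Set, and the likely difference is small. It is a wording point.

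**Conclusion.** The 8.4 numerator rule is wrong as written. It contradicts the AE definition (8.1) and the all-AE primary endpoint (3.4, 9.2.1, 9.3.2), and it ignores the distinction that 9.2.2 draws between all SAEs and drug-related SAEs. Confidence in the contradiction is high, since it rests on the text alone.

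The consequence is conditional: if 8.4 governs the analysis, the primary incidence can only stay the same or fall, it rests on open-label attribution, and Table 1 read literally excludes unexpected events and those that the tumour could explain. The size of that effect on the primary endpoint cannot be determined from the protocol. The phase III SAE pair shows that all-cause and related rates can differ widely, but it does not measure the error in the any-AE rate.

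**What to change.** Reword 8.4 as follows:

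- The definitely, probably and possibly related categories form the numerator of the *drug-related* AE incidence only.
- The primary AE incidence is the number of Safety Set subjects with at least one AE of any causality, divided by all Safety Set subjects. Drug-related incidence is tabulated separately.
- The denominator sentence refers to all subjects in the Safety Set as defined in 9.1.

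One decision should be made openly. AEs are collected from the signing of consent (6.1, 8.1), while treatment-emergent AEs appear only as a secondary measure in 9.2.2 and are not defined. If the primary measure is meant to be limited to treatment-emergent AEs, the amendment should say so and define the term; the correction to 8.4 should not bring that change in unstated.

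The cost is about two sentences and one extra column in the AE tables, plus a definition if the treatment-emergent limit is chosen. No new data are needed, and the change can be made before the SAP is finalised. Headline AE rates may look less favourable than under the related-only rule.
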